**Assessment measures**									
	Anxiety symptoms (GAD-7^a^)			✓		✓		✓	
	Depressive symptoms (PHQ-9^b^)			✓		✓		✓	
	Alcohol consumption risk (USAUDIT-C^c^)			✓				✓	
	Opioid use frequency			✓^d^				✓	
	Stimulant use frequency			✓^d^				✓	
	Cannabis use frequency			✓				✓	
	Alcohol binge frequency (question 3, USAUDIT-C)			✓				✓	
	Alcohol use frequency (questions 1 and 2, USAUDIT-C)			✓				✓	
	Mental well-being (SWEMWS^e^)			✓				✓	
	Readiness to change			✓				✓	
	Self-efficacy: mental health			✓				✓	
	Self-efficacy: substance use			✓				✓	
	Connection to services and supports			✓				✓	

^a^GAD-7: General Anxiety Disorder 7-Item.

^b^PHQ-9: Patient Health Questionnaire 9-Item.

^c^USAUDIT-C: US Alcohol Use Disorders Identification Test-Consumption Scale.

^d^Baseline measure used for study group allocation.

^e^SWEMWS: Short Warwick-Edinburgh Mental Wellbeing Scale.

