##### Depression Symptoms

The PHQ-9 scale is a self-report scale used to assess symptoms of depression and has been validated against diagnostic interviews administered by mental health professionals [28]. The 9 questions are based on the Diagnostic and Statistical Manual of Mental Disorders, 4th edition [26], diagnostic criteria for depressive disorders and scored on a scale of 0 (not at all) to 3 (nearly every day). The total scores range from 0 to 29, with higher scores indicating a worse outcome (ie, greater frequency of depression symptoms). In this study, changes in depressive symptomology from baseline to follow-up at 30 days will be based on the PHQ-9 total scores in both the intervention and control groups.

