##### Alcohol Consumption Risk

The US Alcohol Use Disorders Identification Test-Consumption Scale (USAUDIT-C) is a 3-item self-report scale adapted from the consumption questions in the widely used Alcohol Use Disorders Identification Test (AUDIT). Compared with the AUDIT, the USAUDIT-C includes expanded response options for the first 3 AUDIT questions—from 5 to 7 categories—to allow for more precise measurements in accounting for differences in standard drink sizes and cut-off limits [29]. Although the USAUDIT-C was primarily adapted for US contexts, we believe the expanded response options will also allow for a more precise assessment of adherence to guidelines in drinking frequency (question 1), drinking quantity (question 2), and binge drinking (question 3) within Canadian contexts. For questions 1 and 3, scoring ranges from 0 to 6, where 0 represents “Never” and 6 represents “Daily” frequency. For question 2, scoring ranges from 0 to 6, where 0 represents “1 drink” and 6 represents “10 or more drinks” on a typical day when drinking. The total scores summed from all 3 questions range from 0 to 18, with higher scores indicating a worse outcome (ie, higher-risk level of excessive or harmful alcohol consumption). In this study, changes in alcohol consumption risk from baseline to follow-up at 30 days will be based on the USAUDIT-C total scores in both the intervention and control groups.

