##### Substance Use: Alcohol Use Frequency

Changes from baseline to follow-up at 30 days will be based on the responses to questions 1 and 2 of the USAUDIT-C in both the intervention and control groups.

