The general approach for analyzing all the types of study outcomes separately (including the 3 primary end points and the secondary end points) will be the generalized linear mixed-effect models (GLMMs) for clustered measures, with the randomization block as the clustering variable. These models can handle a wide range of outcome types, including continuous, binary, ordinal, and count, and can account for the correlations among observations within the same cluster. Specifically, we will analyze each primary end point using a linear mixed-effect model, a special case of the GLMM. For secondary outcomes, we will use linear mixed-effect models to analyze mental well-being measures and readiness to change measures, mixed logit models to analyze the connection to services and support-related measures (binary: yes or no), mixed-effects quasi-Poisson regression models with the log link (a special case of GLMMs) for substance use frequency measures, and mixed-effects proportional odds ordinal logistic regression (another special case of GLMMs) for self-efficacy measures. The treatment effect on an outcome at 30 days will be assessed using a GLMM with the treatment allocation as the main explanatory variable and with adjustment for baseline outcome assessment value and other baseline prognostic factors as fixed effects and the randomization block as a random effect. By properly specifying the GLMM, a wide range of scientific hypotheses can be tested, including the primary ones regarding treatment effect estimation. The quality of statistical inferences will be substantiated through rigorous model checking and validation techniques. When statistical models assume that residuals at certain levels follow normal distributions, this assumption will be checked using a normal probability plot, in which the ranked residuals are plotted against corresponding points on a normal distribution curve. When substantial departures from the normal residual assumption are found, robust empirical SE estimates that are valid with nonnormal residuals will be used for statistical inference. We will use SAS software (version 9.4; SAS Institute Inc) and R (version 4.3.1; R Foundation for Statistical Computing) for the statistical analyses of our primary and secondary outcomes. Subgroup analysis will be performed using the GLMM on the subsets of data formed by the subgroup.

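### The secondary outcome 'alcohol use frequency' includes a drinking-quantity item, and the 0-6 alcohol category codes are assigned to a log-link count model, so the reported effect would not be a ratio of drinking occasions

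*Protocol article*

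**What the plan says.** The section Alcohol Consumption Risk describes the three USAUDIT-C items as "drinking frequency (question 1), drinking quantity (question 2), and binge drinking (question 3) within Canadian contexts". Each has seven response categories. On the coding it says: "For questions 1 and 3, scoring ranges from 0 to 6", running from never to daily. Question 2 is also coded 0 to 6, but there 0 stands for one drink and 6 for ten or more on a typical drinking day.

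The section Substance Use: Alcohol Use Frequency then states: "Changes from baseline to follow-up at 30 days will be based on the responses to questions 1 and 2 of the USAUDIT-C". Table 1 repeats the definition: "Alcohol use frequency (questions 1 and 2, USAUDIT-C"). Binge frequency is defined from question 3 alone. The overview of secondary outcomes lists both among the substance use frequency measures.

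For that family, Statistical Analysis specifies "mixed-effects quasi-Poisson regression models with the log link (a special case of GLMMs) for substance use frequency measures". The same paragraph names ordinal outcomes as a type its models can handle, and assigns mixed-effects proportional-odds regression to the self-efficacy items, which are scored 1 to 5.

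On a separate instrument, Depression Symptoms says of the PHQ-9: "The total scores range from 0 to 29, with higher scores indicating a worse outcome".

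**The concern.** There are two linked problems.

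- **Definition.** One section calls question 2 quantity; another makes it part of an outcome named frequency. The secondary outcomes are meant to show in which areas the app acts. Drinking less often and drinking less per occasion are different effects, and this definition does not keep them apart.
- **Scale and model.** A log-link count model gives a ratio of means. That ratio is readable as relative frequency when the response counts days or occasions. Here the only documented response is a category code, so the ratio compares average codes. A reader of the results would naturally take it for a relative change in how often students drink or binge.

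**Working it through.** **1. Definition, passages side by side**

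| Item | What the article says it measures | Where it is used |
|---|---|---|
| Question 1 | Frequency, code 0 (never) to 6 (daily) | Alcohol use frequency |
| Question 2 | Quantity, code 0 (one drink) to 6 (ten or more) | Alcohol use frequency |
| Question 3 | Binge drinking, code 0 (never) to 6 (daily) | Binge frequency |

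The coding is consistent with the article's stated total for the instrument: 3 items × 6 = 18. The article does not say how questions 1 and 2 are combined, so each possibility has to be considered:

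- *Sum of codes.* Daily drinking of one drink gives 6 + 0 = 6. Frequency code 1 with quantity code 5 also gives 1 + 5 = 6.
- *Product of codes.* Daily drinking of one drink gives 6 × 0 = 0, the same as never drinking.
- *Recoded days × drinks.* This is volume consumed, not frequency.
- *Two separate analyses.* Question 1 is then sound, but the result for question 2 is still labelled frequency.

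Under none of the four does question 2 contribute information about frequency.

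**2. Size under one possibility (sum), with assumed distributions**

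Assume the question 1 and question 2 codes are each uniform on 1 to 6 in the control arm (mean 3.5 each). In the intervention arm question 1 is identical and question 2 is one code lower (mean 2.5).

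- Expected ratio for the sum: (3.5 + 2.5) / (3.5 + 3.5) = 6/7 = 0.857.
- A simulated quasi-Poisson fit with 524 per arm (the article's evaluable number), without baseline adjustment or block effect, gives 0.86 (95% CI 0.82 to 0.90).
- The same fit on question 1 alone gives 1.00 (0.94 to 1.06).

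So an effect confined to quantity appears as a clear effect on 'frequency'.

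**3. Ratio of mean codes against ratio of days**

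Binge frequency is question 3 alone, so no combination rule enters. The article does not give the intermediate categories. Two assumed mappings of codes 0 to 6 to days per 30 show the range:

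- unequal spacing: 0, 0.5, 1, 4.3, 10.7, 21.4, 30
- equal spacing: 0, 5, 10, 15, 20, 25, 30

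Take a control arm with half the students at code 3 and half at code 6, so the mean code is 4.5. Mean days are (4.3 + 30)/2 = 17.15 under unequal spacing and (15 + 30)/2 = 22.5 under equal spacing.

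| Intervention arm | Ratio of mean codes | Ratio of days, unequal spacing | Ratio of days, equal spacing |
|---|---|---|---|
| The half at code 3 move to code 2 | 4.0/4.5 = 0.89 | 15.5/17.15 = 0.90 | 20/22.5 = 0.89 |
| The half at code 6 move to code 5 | 4.0/4.5 = 0.89 | 12.85/17.15 = 0.75 | 20/22.5 = 0.89 |

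The model's estimate is 0.89 in both rows. Under unequal spacing the change in days is a 10% fall in one and a 25% fall in the other. The two scales agree only if the categories are equally spaced from never upwards. For question 2 equal spacing would not be enough, because code 0 means one drink, so a ratio of mean codes is not a ratio of drinks.

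**4. PHQ-9 range (clerical)**

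Nine items scored 0 to 3 give a maximum of 9 × 3 = 27, not 29. The parallel GAD-7 figure is right: 7 × 3 = 21.

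**The case against.** The best defence is that the article is a condensed account. A full analysis plan may analyse questions 1 and 2 separately, or recode responses to days or volume, and a log-link count model would be reasonable for a volume. That could answer the scale problem. It would not answer the label, which is fixed in two places and conflicts with the description of the instrument.

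It is also fair to say that inference suffers little. Quasi-Poisson estimates the dispersion, so a test of equal mean codes can be approximately valid. One simulation with seven-category codes, an assumed distribution, proportional odds true, 524 per arm, baseline adjustment and 400 runs gave type I error of 5.5% for quasi-Poisson and 5.3% for proportional odds, with power of 69% and 73%. This stands. The harm is to meaning, and proportional odds carries an assumption of its own.

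Several stronger readings are tempting but not supported:

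- *That the items are summed, so a fall in frequency offset by a rise in quantity shows as exactly no change.* The article gives no combination rule.
- *That a step from code 1 to 2 is estimated as a doubling and from 5 to 6 as a 20% rise.* The model compares arm means at 30 days adjusted for baseline, not individual steps.
- *That the ceiling of 6 contradicts the model.* Quasi-Poisson specifies a mean and a mean-variance relation; a bounded score is not ruled out.
- *That quasi-Poisson, having no full likelihood, leaves these outcomes outside the missing-data strategy.* The likelihood wording is loose here. With one post-baseline outcome per participant, a correct mean model and data missing at random given the covariates, the estimate remains consistent.
- *That the cannabis, opioid and stimulant measures share the problem.* Their response formats are in an appendix that is not shown.

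**Conclusion.** The point holds for the alcohol items. The inclusion of a quantity item in an outcome named frequency is a direct contradiction within the article and depends on no assumption. The mismatch between code and model holds on what the article states: a 0-6 code is the only scale given and no recoding is mentioned. An unseen recoding would remove that second part for question 1 and for binge frequency.

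The figures 0.86 against 1.00, and 0.89 against 0.75 to 0.90, rest on assumed distributions and an assumed spacing of categories. They show the kind of misreading that is possible, not its likely size in this trial.

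The consequence is limited to the interpretation of secondary outcomes. The primary USAUDIT-C total, analysed with a linear mixed model, and the sample size are untouched. The PHQ-9 maximum is a clerical slip that changes no analysis and adds no weight to this point.

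**What to change.** 1. Define alcohol use frequency as question 1 alone, in the outcome section and in Table 1. Report question 2 as a separate outcome named drinking quantity.
2. Analyse questions 1, 2 and 3 with the mixed proportional-odds model the plan already uses for self-efficacy. Its drawback is the proportional-odds assumption, which should be checked, with the alternative named in advance. If quasi-Poisson is preferred, first state the recoding of each category to days or drinks, and describe the effect as a ratio on that scale.
3. Leave the cannabis, opioid and stimulant models as they are unless their response formats prove to be coded categories too.
4. Separately, correct the PHQ-9 range to 0 to 27.

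The cost is wording. The items are already collected individually, no sample-size figure changes, and the article says analysis starts only at the end of the trial on a blinded database, so the definitions can be settled before any comparison of the arms.

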### Randomization and Study Arms

A study participant is defined as an individual who has completed the baseline survey and has been randomly assigned into either the control or intervention group. Participants are randomized using a stratified block randomization function built into the app. The randomization list for the built-in function was created using the web-based stratified block randomization list creator in the clinical trial software Sealed Envelope (Clerkenwell Workshop) [35]. To ensure that each arm of the randomized trial contains an equal number of participants endorsing a history of substance use, participants will be assigned to either group A (substance use: any medical opioid use, nonmedical opioid use, or nonmedical stimulant use) or group B (nonsubstance use), based on their answers to the opioid and stimulant use questions in the baseline survey. After being stratified into group A or group B, individuals are then automatically randomly assigned (via the randomization list embedded into the app) to either the control or intervention arm of the trial using a 1:1 ratio in blocks of 10.

Those randomized into the control group will receive a message saying that they will be asked to complete an additional survey at 30 days and will only receive full access to the app after that. During the 30-day study period, the control group participants will receive a restricted version of the app that only permits access to the following: an introduction video with several students providing a broad overview of the different aspects of the app and its potential value, several onboarding slides with a short summary of the main app components, and baseline and follow-up assessment surveys plus reminder notifications to complete those surveys. Participants randomized into the intervention group will receive immediate access to the full *Minder* app.

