### Data Analysis Plan

#### Statistical Analysis

The primary analysis will be intention to treat (ITT) to estimate the causal effects of the assignment to treatment on the trial outcomes for all participants. A participant within the study is defined as an individual who has completed the baseline assessment survey and has been randomized into either the control or intervention group. The analysis will consider the following 2 features of the trial design: 3 primary end points and the method of randomization. The effects of some of these design features (ie, randomized blocks) are expected to be small and statistically nonsignificant. Nonetheless, we will use multilevel regression and SAS (version 9.4; SAS Institute Inc) and R (version 4.3.1; R Foundation for Statistical Computing) software in our analyses to control for these effects.

Before any testing, we will compare the baseline differences between the randomization groups on demographic (eg, sex, gender, and ethnicity), socioeconomic (eg, year of study), and personal risk variables (eg, mental health diagnoses and use of mental health treatments). Any baseline prognostic variable with a standardized difference between the groups of Cohen *d*>.05 will be considered a candidate variable to control for in the analysis. The selection of Cohen *d*>.05 is arbitrary: there is no accepted threshold to determine a meaningful difference between the 2 groups. However, this is a very small effect and indicates approximately a 4% nonoverlap between the 2 populations.

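### Randomization is stratified by opioid/stimulant use, yet no model names the stratum as a term, and the d>.05 screen essentially cannot bring it in; the cost is small and the repair is free

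*Protocol article*

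**What the plan says.** **Design.** *Randomization and Study Arms* gives the aim of the stratification: "To ensure that each arm of the randomized trial contains an equal number of participants endorsing a history of substance use". It then describes the allocation: "After being stratified into group A or group B, individuals are then automatically randomly assigned", to the "control or intervention arm of the trial using a 1:1 ratio in blocks of 10". Each block therefore lies wholly inside one stratum. A footnote to Table 1 marks the opioid and stimulant items: "Baseline measure used for study group allocation".

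**Analysis.** *Statistical Analysis* states: "The analysis will consider the following 2 features of the trial design: 3 primary end points and the method of randomization". The only element of the randomization method it then names is the block: "The effects of some of these design features (ie, randomized blocks) are expected to be small and statistically nonsignificant". Baseline variables that differ between arms by Cohen d>.05 become candidates for adjustment. The separate models for all primary and secondary outcomes contain treatment, the baseline value of the outcome and "other baseline prognostic factors as fixed effects and the randomization block as a random effect". The global test uses a marginal multivariate regression on PHQ-9, GAD-7 and USAUDIT-C, for which no block, stratum or covariate is named.

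**The concern.** A factor used to stratify randomization normally belongs in the analysis model. Stratification removes between-stratum variation from the treatment comparison, and a model that ignores the stratum leaves that variation in the residual, so the reported standard error is too large. Here the article undertakes to reflect the method of randomization but carries over only the blocks.

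The screen makes this worse. It selects on observed imbalance, and stratification is there to prevent imbalance. A rule of this kind admits covariates that differ by chance and passes over the one factor chosen in advance.

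Attrition is a second issue. The plan allows for 30% loss and relies on data being missing at random given what is in the model. If dropout depends on stratum and arm together, a model without the stratum can leave some bias.

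**Working it through.** **1. The plan's own figures.** Two-sided alpha 0.05/3, 80% power, d=0.2: n = 2(2.394+0.842)²/0.2² ≈ 524 per arm, as stated (alpha .02 would give 502). Attrition: 524/0.7 = 748.6, stated as 748. Adding a stratum term changes neither figure.

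**2. Can the screen select the stratum?** An unfinished block of 10 leaves an imbalance of at most 5 people. With 748 per arm and group A prevalence p (not given in the article, so varied), the worst-case d is (5/748)/√(p(1−p)):

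| p | worst-case d |
|---|---|
| 1% | .067 |
| 2% | .048 |
| 5% | .031 |
| 10% | .022 |
| 20% | .017 |
| 30% | .015 |

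Setting d=.05 gives p(1−p) = (0.00668/.05)² = .0179, so p ≈ 1.8%. In 4,000 simulated allocations per prevalence, d exceeded .05 in none at 3% or more, in 0.2% at 2% and in 1.2% at 1%. For comparison, an unstratified covariate has SE(d) ≈ √(2/748) = .0517 and passes |d|=.05 by chance about 33% of the time.

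**3. Effect on the standard error.** Simulation assumptions: N=1496, stratified blocks of 10, 30% random dropout, no treatment effect, baseline outcome adjusted, and a stratum difference beyond baseline expressed in residual SDs; 1,000 runs per scenario. Mean reported SE of the treatment effect:

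| group A, stratum effect | neither term | random block | stratum fixed |
|---|---|---|---|
| 10%, 0.5 SD | .0500 | .0496 | .0495 |
| 20%, 0.5 SD | .0504 | .0497 | .0495 |
| 30%, 0.8 SD | .0524 | .0502 | .0495 |

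- Against the planned random-block model, the largest reduction is 1 − .0495/.0502 = 1.4%.
- Against neither term, the reduction runs from 1 − .0495/.0500 = 1.0% to 1 − .0495/.0524 = 5.5%. In the weakest scenario (5%, 0.3 SD) it is negligible: .0496 to .0495.
- In the last row the random block recovers (.0524−.0502)/(.0524−.0495) = 76% of the gap.
- In that row the actual spread of the estimates barely moves (.0498, .0494, .0495), so the omission mainly makes the reported SE too large.
- Rejection rates at a nominal 5% were .038 to .064 over all models and scenarios. The .064 arose where the models with the stratum gave .061 and .062, so it is not due to the omission.

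**4. Bias under differential dropout.** Assumed: 15% in group A, a 0.6 SD difference, 40% dropout in group A intervention and 25% elsewhere, no true effect.

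- Group A share among completers, intervention: .15×.60/(.15×.60+.85×.75) = .09/.7275 = .1237. Control: .15.
- Bias with neither term and no baseline adjustment: (.1237−.15)×0.6 = −0.016 SD.
- Random block only, no baseline adjustment: −0.0126 SD relative to the stratum-fixed model, by simulation.
- Random block plus the planned baseline adjustment, with the 0.6 SD difference present at both times and baseline–follow-up correlation .5, .6 or .7: −0.0070, −0.0058 and −0.0043 SD.

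Relative to the target d=0.2, these are 0.0126/0.2 = 6% without baseline adjustment, and 0.0070/0.2 = 3.5% down to 0.0043/0.2 = 2% with it. A harsher assumption (30% in group A, 45% dropout in the one cell) gives −0.0365 with neither term and −0.026 with random block, both without baseline adjustment.

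**The case against.** **The stratum is not wholly absent.** Blocks are nested in strata, so the random block carries stratum information and recovers most of the standard-error gap. The opioid and stimulant models also adjust for baseline values that define the stratum. This stands. A reader might infer that the analysis ignores the stratum altogether; the separate models do not. The block is a weaker substitute for bias, however: in the 15% scenario without baseline adjustment it removes only about a fifth, (.0157−.0126)/.0157.

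**The screen need not be the only route.** The article makes variables with d>.05 candidates. It does not say that nothing else may enter, and a final covariate list may sit in an analysis plan that is not shown. This stands in part. But the article does state a model and a screening rule, and as stated neither brings in the stratum.

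**The global test names no covariates at all**, not even baseline scores, and follows a general commitment to multilevel regression that controls for design effects. This is fair. The text does not exclude the stratum there; it leaves it unnamed in the test that decides whether the separate tests follow.

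**The dropout scenario is assumed.** The article gives no prevalence for group A, no prognostic strength and no sign that dropout concentrates in one cell. Group A includes medical opioid use and is not defined by alcohol. This stands. A reader might infer material bias, perhaps a tenth of the target effect, or invalid tests. The documents support neither: the planned baseline adjustment reduces the bias to a few percent of d=0.2, and type I error shows no inflation under random attrition.

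**Conclusion.** The point holds in a limited form. The trial stratifies on a factor that no model names, the random block stands in for it only partly, and the stated screen essentially cannot select it among all randomized participants unless group A is below about 2%. It would be too strong to say that the screen could never select it, since that depends on a prevalence the article does not give.

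The expected cost is a slightly conservative analysis: a reported standard error up to about 1.4% above what the planned mixed model would give with the stratum added, and more where neither term is used. Residual bias of roughly 0.004 to 0.013 SD is possible if dropout differs by stratum and arm, depending on baseline adjustment. These sizes rest on assumed prevalence (5% to 30%), prognostic strength (0.3 to 0.8 residual SD) and, for the bias, the 15% dropout scenario above. This is a free improvement of low severity.

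**What to change.** Prespecify the A/B stratum as a fixed effect in the global marginal model and in each primary and secondary mixed model. State that it enters regardless of the d>.05 screen, and keep block as a random effect within stratum.

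The cost is one sentence of text and one binary covariate already used for allocation. No new data are needed, and the sample size stays at 524 evaluable and 748 randomized per arm.

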### Sample Size and Power

The sample size calculation for a small effect assessed by the PHQ-9, GAD-7, and USAUDIT-C was calculated using an effect size defined by Cohen *d*=Δ/σ, where Δ is the group mean difference at the completion of the study and σ is the (pooled) within-group SD. For a small effect size (Cohen *d*=0.2), the sample size required to have 80% power at the level of significance *P*=.02 (0.05/3 primary outcomes) is 524 in each group. Assuming a 30% attrition rate, we require 748 participants in each group. To account for a conservative estimate of a small effect size and a 30% attrition rate, we estimate that a minimum of 748 randomized participants will be needed for each study group, totaling at least 1496 participants.

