In addition to the primary analysis using ITT, we will conduct a secondary analysis to evaluate the Complier Average Causal Effect (CACE) of the intervention. The primary analysis using ITT estimates the causal effects of treatment assignment on the trial outcomes for all participants, regardless of whether those assigned to the intervention actually use the *Minder* app (ie, complying with the treatment assignment). The results from the ITT analysis will be useful to policy makers and inform the effects of applying the treatment program to the population. Although ITT analysis is informative and valid, one limitation of the ITT analysis is that it estimates the program effectiveness rather than method efficacy. The program effectiveness depends on the proportion of compliers, which can change (eg, students change their willingness to use the intervention after they learn that the intervention works). Thus, to complement this approach, we will also conduct a CACE analysis that will focus on the intervention efficacy of those who actually use the e-intervention. The CACE analysis in conjunction with the abovementioned ITT analysis will provide a more complete picture of the intervention effect. By identifying who uses and benefits from the intervention, the trial can yield findings of direct interest to the scientific community and individual students. To overcome the challenge that the study participants’ compliance and app use behaviors are self-selected in nature and not randomized, we will use the principal stratification approach to estimate the CACE effects on multiple end points in RCTs with treatment noncompliance [36] and the dose-response relationship between the extent of app use (eg, completed Chatbot Activities and number of contacts with Peer Coach) and intervention effect [44]. Given the diverse nature of the target population combined with the self-guided use of intervention components, we also plan to examine heterogeneity in treatment effects using a series of exploratory analyses that use sociodemographic (eg, gender and year of study) and assessment data (eg, symptom level on PHQ-9 and GAD-7) collected at baseline to examine the impact of the *Minder* app on key subgroups.

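### The plan aims to examine heterogeneity of treatment effect, but its only stated subgroup method, a separate model in each subset, neither estimates nor tests the difference between subgroups

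*Protocol article*

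**What the plan says.** Two statements in the protocol article, both under Statistical Analysis, bear on this point.

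- **Aim.** The investigators write that "we also plan to examine heterogeneity in treatment effects using a series of exploratory analyses". The variables named as examples are gender, year of study and "assessment data (eg, symptom level on PHQ-9 and GAD-7) collected at baseline to examine the impact of the" app on key subgroups. No method is attached to this statement.
- **Method.** "Subgroup analysis will be performed using the GLMM on the subsets of data formed by the subgroup". This is the only sentence that says how subgroups will be analysed.

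The model to be run in each subset is the general one, "with the treatment allocation as the main explanatory variable and with adjustment for baseline outcome assessment value" and other prognostic factors, plus a random effect for randomization block. The article mentions no treatment-by-subgroup term and no other formal comparison between subgroups.

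**The concern.** Heterogeneity is a difference between subgroup effects. A model fitted to one subset alone estimates the effect in that subset and nothing else. A set of such models therefore yields several treatment effects, each with its own p-value, but no estimate of how far they differ and no test of that difference.

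In practice the gap tends to be filled by contrasting p-values: significant in one subset, not in the other, so the app seems to work for one kind of student only. A trial sized for a small overall effect has limited power within subsets, so this pattern arises often when the effect is the same in everyone. The Conclusions section hopes that subgroup analyses will help to show how to improve the app and extend it to other student populations. A false pattern could misdirect that work.

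**Working it through.** **Inputs from Sample Size and Power.** The planned effect is "For a small effect size (Cohen *d*=0.2"), standardised so that "σ is the (pooled) within-group SD". The article gives "the sample size required to have 80% power at the level of significance" printed as .02, which it derives as "0.05/3 primary outcomes) is 524 in each group".

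**Assumptions, because the article does not give these figures.** Two-sided tests; .05 within each subset; two subsets split 50:50 or 30:70; the same true effect in everyone; baseline/follow-up correlation r of 0.5 to 0.7.

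**1. Reproduce the plan's sample size.** n per arm = 2(z₁₋α/₂ + z₀.₈)²/d². With α = 0.05/3 this is 2(2.394 + 0.842)²/0.04 = 523.5, so 524. The plan's figure is reproduced, and the two-sided reading is confirmed.

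**2. Power within a subset, no baseline adjustment.** Power ≈ Φ(d√(m/2) − 1.96), with m completers per arm in the subset.

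- 50:50, m = 262 in each: 0.2√131 = 2.289, so power is 0.629 in both.
- 30:70, m = 157.2 and 366.8: 0.2√78.6 = 1.773 and 0.2√183.4 = 2.709, so power is 0.426 and 0.773.

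**3. Chance that exactly one subset is significant.** p₁(1−p₂) + p₂(1−p₁).

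- 50:50: 2 × 0.629 × 0.371 = 0.467.
- 30:70: 0.426 × 0.227 + 0.773 × 0.574 = 0.540.

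**4. The same with the planned baseline adjustment.** Adjustment reduces the residual SD by √(1−r²), so the working effect becomes 0.2/√(1−r²).

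| r | working effect | power, 50:50 | exactly one, 50:50 | power, 30:70 | exactly one, 30:70 |
|---|---|---|---|---|---|
| none | 0.200 | 0.629 / 0.629 | 47% | 0.426 / 0.773 | 54% |
| 0.5 | 0.231 | 0.753 / 0.753 | 37% | 0.535 / 0.879 | 47% |
| 0.6 | 0.250 | 0.816 / 0.816 | 30% | 0.601 / 0.923 | 41% |
| 0.7 | 0.280 | 0.894 / 0.894 | 19% | 0.699 / 0.967 | 31% |

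**5. The interaction test under the same truth.** The unadjusted standard error of the difference is √(2/(524f) + 2/(524(1−f))), with f the fraction in the first subset. In 400,000 simulated trials with a uniform d=0.2, the test at .05 signalled a difference in 4.95% at 50:50 and 5.05% at 30:70.

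**6. What the interaction test can detect.** At 50:50 the standard error is √(4/262) = 0.1236. For a true between-subgroup difference of d=0.2, 0.2/0.1236 = 1.619, which gives power of about 37% unadjusted.

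**The case against.** The case for leaving the text alone has real substance.

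- **Separate fits do not rule out a valid test.** For disjoint subsets, (b₁ − b₂)/√(SE₁² + SE₂²) is a standard test of heterogeneity. In a simulation with the inputs above it had a false-positive rate of about 5%. This stands: the fault is not subset fitting in itself but that no between-subgroup comparison is specified.
- **No p-value contrast is announced.** A reader might infer that the investigators will declare subgroup effects by whether each subset reaches significance. The document does not say so, and it sets no subgroup alpha. The percentages above describe what follows if that contrast is made, not a rule in the plan.
- **The unadjusted figures are an upper end.** The planned model adjusts for baseline, which lowers them. This also stands, and the adjusted range is the one to use.
- **Nothing decisive rests on these analyses.** A reader might infer that the trial will use them to decide for whom the app works. The text calls them exploratory and speaks only of hopes.
- **Other complaints one might add are weak.** That PHQ-9 and GAD-7 will be cut into categories is an inference, since no cut-points are given. Thin randomization blocks within subsets are no quantified loss, because block is a random effect that the plan expects to be small.

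The details of comparing subsets could also be left to an analysis plan not shown. But the article is not silent: it names a method, and that method does not produce the quantity its aim requires. Calling the work exploratory excuses low power and multiplicity, not the lack of any estimate of the target.

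**Conclusion.** The point holds. The stated aim is a difference between subgroup effects, and the stated method gives no estimate or test of one. If significance is contrasted across two subsets, a uniform effect of the planned size would look like a subgroup finding in about 19–37% of trials at a 50:50 split and 31–47% at 30:70, with baseline adjustment at an assumed correlation of 0.7 to 0.5. Without adjustment the figures are 47% and 54%. All are well above the 5% of an interaction test. They rest on the assumed splits, the .05 level and the correlation, none of which the article gives.

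The consequence is confined to exploratory analyses. The intention-to-treat analysis, the global test and the Hochberg step are unaffected. The change is worth making because it is nearly free.

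**What to change.** Replace the subset sentence with wording to this effect: subgroup analyses will fit the GLMM to the full data set with a treatment-by-subgroup interaction; the interaction estimate will be reported with its confidence interval and p-value; subgroup-specific effects will be taken from that same model and presented descriptively. Preferably enter baseline PHQ-9 and GAD-7 as continuous moderators, since both are collected as total scores.

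Add one caution: a non-significant interaction is not evidence that the effect is homogeneous, because power is about 37% for a between-subgroup difference of d=0.2 at 50:50 without adjustment.

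The cost is two sentences of wording. No extra data or participants are needed.
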